## Abstract

Background: Coronavirus disease (COVID-19) vaccine-related side effects have a determinant role in the public decision regarding vaccination. Therefore, this study has been designed to actively monitor the safety and effectiveness of COVID-19 vaccines globally. Methods: A multi-country, three-phase study including a cross-sectional survey to test for the short-term side effects of COVID-19 vaccines among target population groups. In the second phase, we will monitor the booster doses’ side effects, while in the third phase, the long-term safety and effectiveness will be investigated. A validated, self-administered questionnaire will be used to collect data from the target population; Results: The study protocol has been registered at ClinicalTrials.gov, with the identifier NCT04834869. Conclusions: CoVaST is the first independent study aiming to monitor the side effects of COVID-19 vaccines following booster doses, and the long-term safety and effectiveness of said vaccines.

## 1. Introduction

Coronavirus disease (COVID-19) mass vaccination has been a chief priority for health systems globally, which needs to be accelerated in order to control the acute phase of the pandemic [1,2]. Nevertheless, vaccine hesitancy (VH)—which refers to the “delay in acceptance or refusal of vaccines despite the availability of vaccine services”—remains a serious challenge for vaccination strategies worldwide [3,4,5]. In 2019, the World Health Organization (WHO) declared VH as one of the top 10 global health threats, which is nourished by misinformation regarding vaccines’ effectiveness and safety [6].

Aversion to vaccines’ potential side effects is the most frequent cause of VH among various population groups [7,8]. Therefore, a recent systematic review revealed that raising public awareness of vaccines’ effectiveness, and honesty regarding their side effects, are vital strategies to improve vaccine uptake [9].

According to the Strategic Advisory Group of Experts on Immunization of the WHO (SAGE-WHO), distrust in the pharmaceutical industry is a contextual driver of VH, because vaccine manufacturers can be perceived as preferring their financial benefit over public health interest [10]. In both high-income and low-income settings, distrust of the pharmaceutical industry has been consistently and significantly higher among hesitant groups, and this is aggravated by a lack of transparency regarding public health plans [11,12,13].

Public health systems currently experience a novel and a unique challenge, due to the variety of vaccine manufacturers, and the high levels of public awareness about those manufacturers and their marketing strategies [8]. This unprecedented situation is predicted to create what we can refer to as “vaccine selectivity”, where individuals can prefer a certain type or brand of vaccine over others; this situation will increase the pressure on our weakened health systems and economies, and of course it can increase the VH levels as well [14].

The temporary suspension of the Oxford–AstraZeneca vaccine (AZD1222) (AstraZeneca plc, Cambridge, UK) and the Janssen vaccine (Ad26.COV2.S) (Johnson & Johnson (J&J), New Brunswick, NJ, US) due to reports of extremely rare side effects triggered public debates that might have adversely affected vaccination acceptance levels [15,16]. However, although the European and American cdrug regulators declared that the benefits of using these vaccines still outweigh their risks, very little is known about vaccine hesitancy and, probably, selectivity after these incidences [15,17].

Given the projected seasonality of COVID-19 transmission and the increasing number of its variants, vaccine manufacturers launched trials for booster doses that are predicted to be readily available by the fall of 2021 [18,19,20].

Independent (non-sponsored) studies with rigorous methods can successfully lead the unbiased pharmacovigilance efforts of COVID-19 vaccines globally [21,22,23,24,25,26,27,28]. Thus, in view of their independent nature and transparent design, these studies can play a key role in suppressing VH levels by enhancing public confidence in the vaccines.

### Objectives

This project aims to actively monitor the side effects and effectiveness of COVID-19 vaccines worldwide. The primary objectives of the project include:(a)To estimate the prevalence of both local and systemic side effects following each of the COVID-19 vaccines among healthcare workers (HCWs), teachers and academics (TAs), senior adults ≥65 years old (SAs), and minors ≤18 years old (MIs);(b)To evaluate the potential demographic and medical risk factors for the frequency and intensity of side effects;(c)To evaluate the long-term safety of COVID-19 vaccines.

The secondary objectives include:(a)To evaluate the relative effectiveness and safety of COVID-19 vaccines in relation to one another;(b)To evaluate the impact of palliative medications used by the vaccinated individuals for short-term side effect resolution.

## 2. Materials and Methods

### 2.1. Design

This project is composed of three main phases: (a) a cross-sectional survey for the short-term side effects of COVID-19 vaccines; (b) a prospective cohort study for the safety of COVID-19 vaccines following booster doses; and (c) a prospective cohort study for the long-term safety and effectiveness of COVID-19 vaccines.

#### 2.1.1. Phase A

A validated, self-administered questionnaire will be developed and delivered online to the target population groups (HCWs, TAs, SAs, and MIs). In certain circumstances, telephone interviews and paper questionnaires will be used instead of the online questionnaire in order to adapt to the local setting. The questionnaire will inquire about the short-term side effects following either the first dose, the second dose, or both doses of the COVID-19 vaccine. The side effects will be classified as local or systemic, and their onset, duration, and intensity will be self-assessed and self-reported by the participating subjects. This phase is planned to take place until 31 December 2021.

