#### 2.2.1. Inclusion Criteria

HCWs, TAs, SAs, and MIs who received a COVID-19 vaccine in the post-authorization phase;The recently vaccinated individuals who received their vaccine dose within the previous 30 days will be prioritized to be invited for the study, even though the study will not be limited to the recently vaccinated individuals;Participating subjects should be at least 18 years old in order to give their informed consent independently, or in case of the minors (below 18 years old), their caregivers will be asked to give their informed consent.

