#### 2.2.2. Exclusion Criteria

HCWs, TAs, SAs, and MIs who received the COVID-19 vaccines as part of phase III clinical trials.

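### Phase A records side-effect duration once, favours people dosed in the last 30 days and sets no minimum wait, so effects still present at submission have unfinished durations

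*Protocol article*

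**What the plan says.** Section 2.1 of the protocol article describes Phase A as "a cross-sectional survey for the short-term side effects of COVID-19 vaccines". Section 2.1.1 says that the questionnaire covers "short-term side effects following either the first dose, the second dose, or both doses of the COVID-19 vaccine", and that for these effects "their onset, duration, and intensity will be self-assessed and self-reported by the participating subjects".

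On timing, section 2.2.1 says that those who "received their vaccine dose within the previous 30 days will be prioritized to be invited for the study", and adds "even though the study will not be limited to the recently vaccinated individuals". The only exclusion in section 2.2.2 is "HCWs, TAs, SAs, and MIs who received the COVID-19 vaccines as part of phase III clinical trials". Neither section sets a minimum time since the dose.

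The result that depends most directly on how long effects last is secondary objective (b): "To evaluate the impact of palliative medications used by the vaccinated individuals for short-term side effect resolution".

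Three other places matter:
- Section 2.3 lists dates of vaccine doses, onset and duration among the questionnaire items and refers to Table S1, which is not shown.
- Strengths and Limitations acknowledges that the gap between vaccination and survey varies across countries and commits to a subgroup analysis by that gap. It also names recall bias.
- Sections 2.1.2, 2.1.3 and 2.4.2 recontact volunteers about booster side effects and long-term outcomes. None of them describes completing a duration left open in Phase A.

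**The concern.** A duration can be observed in full only after the effect has ended. With one contact, a preference for recent doses and no floor on elapsed time, some respondents will answer while an effect is still present. What they report cannot exceed the time since their dose. If it is analysed as a completed duration, the error runs one way, towards shorter effects. It is largest for long-lasting effects and for people who answer soonest.

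Two results are exposed: the description of how long side effects last, and the evaluation of palliative medication, where apparent resolution would depend partly on how early people answered.

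Recall and truncation also pull in opposite directions. Recall worsens as time since the dose grows, while truncation lessens. A window chosen to help recall therefore makes truncation worse.

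**Working it through.** **Plan's own figure.** The article gives no figure for duration or for elapsed time at survey. Its only computed figure, the sample size of 368-635, has no bearing here. Every distribution below is therefore an assumption.

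**Inputs from the article.** One questionnaire (2.1, 2.1.1); priority to days 0-30 with no lower limit (2.2.1, 2.2.2); enrolment not confined to those days (2.2.1).

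**Assumed.** True duration D is exponential with mean m days and starts at the dose. Time from dose to submission C is uniform on (a, L). The recorded duration is the smaller of D and C.

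**Formulas.**
- Share unfinished: u = m × [exp(−a/m) − exp(−L/m)] / (L − a)
- Recorded mean: m × (1 − u)

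For exponential durations the relative shortfall in the mean thus equals the share unfinished.

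**All answers in days 0-30 (a = 0, L = 30).**
- m = 1: u = 1 × (1 − e^−30)/30 = 3.3%; recorded mean 0.97
- m = 3: u = 3 × (1 − e^−10)/30 = 10.0%; recorded mean 2.70
- m = 7: u = 7 × (1 − e^−4.286)/30 = 7 × 0.9862/30 = 23.0%; recorded mean 5.39

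A simulation of one million draws gave 2.70 and 5.38 for m = 3 and 7. With lognormal durations (log-SD 0.8) the shortfall was 4-13% for medians of 1-3 days and 28% for a median of 7 days.

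**Some respondents vaccinated earlier.** Suppose 70% answer in days 0-30 and 30% in days 30-180. The later group contributes almost nothing to u.
- m = 3: 0.7 × 10.0% = 7.0%
- m = 7: 0.7 × 23.0% = 16.1%

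**Percentages instead of means.** With a = 0 and L = 30, the recorded share lasting over 7 days is the true share × (30 − 7)/30. For m = 7 that is 36.8% × 0.767 = 28.2%. Summarising by percentages does not remove the effect.

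**A floor on elapsed time (illustrative).** Shortfall in the mean:
- 7 days (a = 7, L = 30): m = 3, 3 × (0.0970 − 0.0000)/23 = 1.3%; m = 7, 7 × (0.3679 − 0.0138)/23 = 10.8%
- 14 days (a = 14, L = 30): m = 3, 0.2%; m = 7, 7 × (0.1353 − 0.0138)/16 = 5.3%

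With a 7-day floor the share lasting over 7 days is recorded in full, because everyone has been observed that long. A mean is still cut short.

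**The case against.** The case against has real weight.

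- **The instrument is not visible.** Table S1 may already offer an ongoing or open-ended answer, in which case unfinished durations can be identified. This stands. A reader might infer that the questionnaire lacks such an answer; the article does not show that.
- **The analysis is not spelled out.** A reader might infer from section 2.7 that reported durations are treated as final, because side effects are to be summarised as frequencies and percentages. That section does not say how duration is handled, and it also plans inferential tests. A censoring method can properly sit in an analysis plan, so its absence here is not the point.
- **Duration is not primary.** The primary objectives concern prevalence, risk factors for frequency and intensity, and long-term safety. Secondary objective (a) compares vaccines on safety in general and does not name duration. This stands and limits the reach of the point.
- **The time-span subgroups address it.** They would show that reported duration depends on elapsed time and allow comparison at similar elapsed times. Durations in the earliest subgroup remain cut short, so this is detection and not correction.
- **The calculation leans high.** It places everyone in days 0-30, whereas Strengths and Limitations expects recruits vaccinated in the first half of 2021. Respondents reporting on both doses have also had longer for first-dose effects to end. Both dilute the bias, but neither removes it for the recent doses that are given priority.
- **The window helps recall.** It does, and that is a reason to keep it and deal with truncation in the analysis.

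**Conclusion.** The point holds as a minor one. The features that create unfinished durations are all fixed in the text: one contact, priority to recent doses, no minimum interval, and no recontact described to complete Phase A durations. Unless ongoing effects are identified and handled, descriptive duration and secondary objective (b) are biased towards shorter effects. The primary objectives do not use duration.

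The size is conditional. Under exponential durations starting at the dose and answers spread evenly over days 0-30, the mean falls short by about 3-10% for effects averaging 1-3 days and about 23% for 7 days. With 30% of answers at 30-180 days, the figure at 3 days is about 7%.

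A reader might take the first-week case as the expected bias: with L = 7, the recorded mean is 1.84 for a true 3 days and 2.58 for a true 7 days. The documents do not support that, because the share of respondents answering in their first week is not given. Nor do they support saying that a stated between-vaccine comparison of duration is invalid, since no such comparison is named.

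**What to change.** Keep the recruitment window. Use the dose dates that section 2.3 already collects, together with the submission date, to give each reported dose its elapsed time. Then state one of these as the main approach to duration and resolution and the other as a sensitivity analysis:

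1. **Right-censoring.** Treat an effect still present at submission as censored on that date, and analyse time from onset to resolution, for example by Kaplan-Meier. Confirm that Table S1 has a still-present answer for each side effect, or add one. This assumes that when people answer is unrelated to how long their effect lasts.
2. **Minimum elapsed time.** Limit the duration and resolution analyses to doses given at least a pre-stated number of days before submission, and report the share unresolved at days up to that limit. These shares are fully observed, while a mean would still be shortened.

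Retain the time-span subgroups as a check. Extend the change to Phase B only if its questionnaire can also be answered soon after the booster, which the article does not say.

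Cost: a few lines of analysis wording and possibly one answer option. Under the second approach some recent respondents leave the duration analysis. Responses collected before any new answer option would lack it and need a sensitivity analysis.

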#### 2.1.2. Phase B

A validated, self-administered questionnaire will be developed and delivered online to the volunteers who participated in Phase A and expressed their interest in reporting on their long-term outcomes. The short-term side effects following booster doses will be investigated in this phase. This phase is tentatively planned to take place from October 2021 until April 2022.

#### 2.1.3. Phase C

A validated, self-administered questionnaire will be developed and delivered online to the volunteers who participated in Phase A and expressed their interest in self-reporting their long-term outcomes. The vaccines’ effectiveness and safety will be monitored, and this phase will last for five consecutive years, starting from January 2022.

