### 2.2. Population

In Phase A, a pragmatic approach will be used, tracking each target population group according to individual governments’ distributional plans, which in most countries went from HCWs, to SAs, to TAs, to MIs. The sample of Phases B and C will be pre-identified based on the outcomes of Phase A.

If more than 368 of the Phase A participants show their interest in joining Phase B, no additional recruitment will be required. If less than 368 of the Phase A participants show their interest in participating in Phase B, additional recruitment will be carried out, targeting HCWs who will receive booster doses. In case of the emergence of special side effects after booster doses, additional recruitment of a sample of HCWs will be required.

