#### 2.2.3. Sample Size

The pragmatic sample size for each target group in each country will be calculated using Epi Info ^TM^ version 7.2.4 (CDC, Atlanta, GA, USA. 2020). The formula of population survey studies will be used to achieve a 5% margin of error and a 95–99% confidence level [29]. The expected frequency (outcome probability) is assumed to be 60%, as the prevalence of side effects following COVID-19 vaccines ranged between 62% and 93% in our previous studies [21,22] (Figure 1).

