### 2.7. Analysis

Descriptive statistics will be performed to check the normality of data distribution, and to present the frequencies and percentages of dependent variables (side effects) and independent variables (demographic data, medical anamneses, and COVID-19-related anamneses). Inferential statistics will be performed to evaluate the potential association of each side effect and the suggested demographic and medical risk factors. All tests will be performed using SPSS 27 (IBM Corp, Armonk, NY, USA), and the significance level cutoff will be set at *p* ≤ 0.05 [32].

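### Phase C, and Phase B unless topped up with outside HCWs, rest on opt-in Phase A volunteers; the article names no check or weighting for this selection and does not list it as a limitation

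*Protocol article*

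**What the plan says.** - **Source of the follow-up samples.** Section 2.1.2 sends the Phase B questionnaire to "volunteers who participated in Phase A and expressed their interest in reporting on their long-term outcomes". Section 2.1.3 uses nearly the same words for Phase C: "volunteers who participated in Phase A and expressed their interest in self-reporting their long-term outcomes". Section 2.4.2 describes the interest in question as wanting to self-report long-term side effects. Section 2.2 adds: "The sample of Phases B and C will be pre-identified based on the outcomes of Phase A".
- **Adequacy of Phase B.** Section 2.2 judges this by headcount: "If more than 368 of the Phase A participants show their interest in joining Phase B, no additional recruitment will be required". Below that number, "additional recruitment will be carried out, targeting HCWs who will receive booster doses". There is a second route: "In case of the emergence of special side effects after booster doses, additional recruitment of a sample of HCWs will be required". No outside recruitment is described for Phase C.
- **Analysis.** Section 2.7 plans descriptive statistics "to present the frequencies and percentages of dependent variables (side effects) and independent variables", followed by tests of association with risk factors. It names no comparison of volunteers with non-volunteers and no weighting.
- **Limitations.** Strengths and Limitations lists the varying time since vaccination, with subgroup analysis as the remedy, and recall bias. It does not mention selection by volunteering.

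**The concern.** People opt in by expressing interest in reporting outcomes of the kind the later phases measure. Someone who reacted to an earlier dose may be more willing to keep reporting, or less. If that person also has a different risk of a booster reaction or a long-term problem, the percentage among volunteers differs from the percentage among all Phase A respondents. Response over five annual waves adds a further selection step each year.

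At stake are the Phase B booster rates and primary objective (c), long-term safety. The 368 rule controls random error only. A Phase B sample can meet it and still give a narrow interval around a biased rate.

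**Working it through.** **1. The plan's own figure.** Inputs from section 2.2.3 and the Figure 1 legend: expected frequency p = 0.60, margin d = 0.05, design effect 1.

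With an unlimited population, n = z²p(1−p)/d²:
- 95%: 1.96² × 0.24 / 0.0025 = 368.8
- 99%: 636.9

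The population size is in a figure not shown. With the finite-population formula, 200,000 to 300,000 people give 368.1 to 368.3 and 634.9 to 635.6. The stated 368–635 is therefore reproduced. The calculation assumes simple sampling and has no term for who volunteers.

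**2. Shift in the make-up of the volunteers.** Let r be the volunteering probability of people with an earlier reaction divided by that of people without. The documents give no value for r, so every value below is an assumption. The share of volunteers with an earlier reaction is v = pr/(pr + 1 − p), with p = 0.60 borrowed from section 2.2.3.

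**3. Bias in the booster rate.** This is (v − p) × (b₁ − b₀), where b₁ and b₀ are the booster side-effect risks with and without an earlier reaction. Both pairs used here are assumptions, chosen so that the true rate is 60%: 0.6 × 70 + 0.4 × 45 = 60 and 0.6 × 80 + 0.4 × 30 = 60.

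| r | v | Shift v − p (points) | Bias, 70% vs 45% (× 0.25) | Bias, 80% vs 30% (× 0.50) |
|---|---|---|---|---|
| 1 | 60.0% | 0 | 0 | 0 |
| 1.25 | 65.2% | 5.2 | 1.3 | 2.6 |
| 1.5 | 69.2% | 9.2 | 2.3 | 4.6 |
| 2 | 75.0% | 15.0 | 3.75 | 7.5 |

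If b₁ = b₀, the bias is zero for every r. If r is below 1, the sign reverses: at r = 0.8, v = 0.48/0.88 = 54.5%, and the biases are about −1.4 and −2.7 points.

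**4. When the bias passes the 5-point margin.** Solving for r:
- With a 50-point risk difference, v must reach 70%, so r = (0.7/0.3)/(0.6/0.4) = 1.56.
- With a 25-point difference, v must reach 80%, so r = (0.8/0.2)/(0.6/0.4) = 2.67.

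**5. Sensitivity to p.** At 93%, the top of the prevalence range in section 2.2.3, r from 1.25 to 2 gives only 0.3 to 0.8 points (70% vs 45%) or 0.7 to 1.7 points (80% vs 30%).

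**6. What weighting costs and leaves.** Weighting back to p on earlier reaction removes the bias in step 3. Its design effect is p²/v + (1−p)²/(1−v).

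| r | Design effect | Effective n from 368 | Margin |
|---|---|---|---|
| 1.25 | 1.01 | 364 | 5.04% |
| 1.5 | 1.04 | 354 | 5.10% |
| 2 | 1.12 | 329 | 5.30% |

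An unmeasured factor would still bias the weighted rate. If it is present in 50% of people, adds 20 points to booster risk and has a volunteering ratio of 1.25 to 2, the remaining bias is 20 × (r/(r+1) − 0.5) = 1.1 to 3.3 points.

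**The case against.** The strongest reply is that section 2.7 is a short summary in a journal article. Weights and non-response tables are commonly left to a full protocol or analysis plan that is not shown. That stands to this extent: the lack of a correction can be asserted of this article only. But the opt-in cohort and the 368 rule are design choices stated here. The article also has a limitations section, which gives an analytic remedy for one problem and leaves this one out.

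Several stronger readings are tempting, and the documents do not support them:

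- **That both phases use volunteers only.** This is wrong for Phase B, which has two HCW top-up routes. They do not address selection among senior adults, teachers or minors, and HCWs recruited from outside have no Phase A record to weight from.
- **That participants are chosen on their side effects.** The sentence about Phase A outcomes can simply mean who opted in. The next paragraph counts interested participants.
- **That the error is 5 to 15 points.** That is the shift in the share with an earlier reaction. The error in the booster rate is that shift multiplied by a risk difference, so it is smaller.
- **That an earlier reaction is the main predictor of later ones.** The article does not say so. Its Discussion names dose number and female gender. It shows no link between short-term reactions and long-term safety.
- **That people who decline a booster bias Phase B.** They lie outside its target, which is side effects after a booster.
- **That a booster-versus-earlier-dose contrast would be distorted.** No such contrast is among the objectives or in section 2.7.

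**Conclusion.** The point holds as a risk that the article leaves unmeasured and unnamed; it is not a demonstrated bias. Phase C, and Phase B unless topped up, depend on opt-in, and the stated percentages carry no check on it. Under the assumed inputs with p = 60% and r from 1 to 2, the booster rate is too high by 0 to 7.5 points, against a 5-point margin. Most of these scenarios stay inside the margin; passing it needs a volunteering ratio above 1.56 with a 50-point risk difference, or above 2.67 with a 25-point difference. The direction could also be downward. No figure can be given for long-term outcomes, because the documents state no long-term risk. The change is worth making because the Phase A questionnaire (section 2.3) already collects the information needed. A reader might infer that the correction is free and complete. It needs no new data, but it costs some precision and corrects only for measured factors.

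**What to change.** In section 2.7, for Phases B and C:

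1. Compare volunteers with non-volunteers, and responders with non-responders at each annual wave, on Phase A side effects, age, sex, target group, vaccine and country.
2. Report estimates weighted by the inverse probability of volunteering and responding, modelled on those variables, beside the unweighted ones. A prespecified sensitivity analysis is the minimum.
3. Report directly recruited HCWs without a Phase A record separately.

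In Strengths and Limitations:

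4. Name volunteer selection as a limitation.

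The cost is analysis work on data already planned, and slightly wider intervals (design effect about 1.01 to 1.12 when weighting on earlier side effects). Weighting does not correct unmeasured selection. It restores only the Phase A sample, itself recruited through networks, with snowballing for the adult groups (section 2.4.1), and not the vaccinated population.
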